#### Study conduct

At the beginning, the study participants will complete a long questionnaire (baseline survey). The CG participants will fill their baseline survey as part of the overall study (SOLDEX project). After responding to the baseline survey, IG participants will begin to attend the day activity service meetings once a week. The CG participants will receive home care services as usual and other social and health care services if needed. The three-month and six-month follow-up surveys will be gathered from both intervention and control group participants. Three months is considered as a sufficient time for the first follow up due to the intensity of the service and the functional capabilities of the participants. The follow-up questionnaire is a short version of the baseline survey including relevant measurements and questions for examining the effectiveness of day activity service in terms of the outcome measures. If the study participants do not return the follow-up survey, they will be called and encouraged to continue the study if possible. Throughout the study, the study participants are offered assistance in filling in the survey in case of visual impairment, for example. At the time of follow-up surveys, IG participants will also be interviewed with ASCOT-tool (Fig. 1.)

#### Outcomes and variables

The primary outcome of the trial is social inclusion, which is measured with the Experiences of Social Inclusion Scale (ESIS) [20]. Secondary outcomes are loneliness and social care related quality of life. Loneliness is measured with De Jong Gierveld Loneliness Scale [21] and single question: How often do you feel lonely? The response options for the single question are: “never”, “very rarely”, “sometimes”, “fairly often”, and “all the time”. Social care related quality of life is measured with Adult Social Care Outcomes Toolkit (ASCOT) [22, 23]. In addition, exploratory outcomes are social networks (LSNS-6 [24]), social support (MOS-SSS [25]), sense of security (single question: How safe are you feeling your life now?), unmet needs related to activities of daily living and instrumental activities of daily living [3] and general quality of life (EUROHIS-QOL 8-item [26]).

Perceived effectiveness is measured in the follow-up surveys for IG participants with two questions: 1. How useful do you find the day activity service for yourself? 2. How meaningful do you find the day activity service for yourself? A five-point Likert scale is used with the following response options: “Very useful/meaningful”, “useful/meaningful”, “neither useful/meaningful or useless/meaningless”, “useless/meaningless”, “very useless/meaningless”.

Changes in life situation or participation during the trial are asked about in the follow-up surveys. Indicators are health or functional ability status, family situation, social relationships, hobbies or other activities, and other changes. Options for answers are “No changes”, “Yes, positive changes”, “Yes, negative changes” and “Yes, both positive and negative changes” (see [27]).

Background variables are collected only in the baseline survey including age, sex, education, income, marital status, native language, living environment, form of housing, cohabitation status, and informal caring status. Other variables and measurements used in the baseline survey are material deprivation (seven items [28]), ability to make ends meet, access to services (health and social care, transport, other services), adequacy of social and health care services, access and use of internet and digital devices, environmental and neighbourhood satisfaction, safety and security in home and surrounding environment, ageism, abuse [29], and access and participation in voting.

Information about the intervention group members’ participation in the day activity service is provided by the municipalities after the six-month trial period.

#### Statistical analysis

First, descriptive analyses will be conducted to indicate similarities and differences between baseline characteristics in the IG and in the CG. The chi-square test is used to compare categorical variables. Continuous variables will be compared using t-test (normal distribution) and Mann-Whitney U test (non-normal distribution).

Intention-to-treat analyses will be performed primarily and for all outcomes. In addition, per-protocol analyses are used in a supplementary sense. Results of the categorical outcomes will be presented through percentages and continuous outcomes through mean scores and standard deviations or medians and quartiles. To evaluate the effectiveness of the intervention, the data will be analysed using suitable methods for correlated panel data such as mixed effect modelling or generalized estimating equations modelling [30]. Methods of multiple imputation will be used if necessary [31]. The challenges of non-randomization will be taken into account using statistical methods, such as propensity score weighting [32], if necessary.

Subgroup analyses will be performed for age, sex, frequency of participation, research area (two areas) and duration of the intervention (2–4 hours/6 hours). In addition, knowledge on tailoring the group activities learned from interviews with professionals (see Process evaluation) will be utilized in the analyses if necessary.

The data will be reported following the CONSORT guidelines [33].

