**Fig. 1 Fig1:**
[figure not shown]
Flow diagram of the study design

The study is conducted in Finland in one municipality and one social welfare and health care joint authority consisting of seven municipalities. There are approximately 2300 older home care clients in the research areas. As of January 2022, 210 of the older home care clients in the research areas had been granted access to the day activity service. According to the professionals responsible for the day activity service, the number of participants has somewhat reduced during COVID-19 pandemic. The research areas include both urban and rural residential districts. The day activity service is carried out across 12 municipalities, villages, or residential areas.

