### Description of the intervention

The intervention is targeted at older home care clients who are not able to participate in other activities because of their poor health or functional ability. The day activity service is a complex intervention which means that it has multiple aims and there is variation in how it is carried out in different settings. The principle aim of the day activity service is to support the older home care clients’ ability to live in their own homes by promoting their health and wellbeing, maintaining their physical, psychological, and social functional ability and by enhancing social inclusion. More specifically, the intervention has aims to; maintain memory, promote social interaction, provide peer support, and reduce loneliness and sense of insecurity.

The day activity service is an additional service to the regular home care services and takes place in local day activity centres or other places once a week. It is a group-based intervention, and the duration of one meeting is from 2 to 6 hours. The intervention includes rehabilitative and preventive activities such as physical exercising, outdoor activities, thematic discussions, activating memory, listening to music, having lunch and coffee together with group participants. The day activity service is tutored by practical nurses or home helpers. In the study sites, there are day activity groups of 2 hours, 3 hours, 4 hours, and 6 hours. There is also variation in the content and activities of the intervention. A payment per meeting is between 5 to 23 euros depending on the duration of the service. Transport is arranged if necessary, paying for a local bus ticket.

Home care clients need to apply for the service and get a service decision on it to take part in the day activity service weekly. The criteria for the decision are i) not able to participate in other activities produced by municipalities, private sector or third sector, and ii) is capable of attending group activities. Severe memory disorder can prevent participation, for example.

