### Quasi-experimental trial

#### Participants, selection criteria and recruitment

The target sample size for the intervention study is 200 participants (100 IG + 100 CG) based on previous research with similar study designs (e.g., [19]) and directional sample size calculations. We accepted an alpha risk of 0.05% and a power of 80% at an effect size of 0.5. A theoretical sample of 64 participants in the IG and 64 participants in the CG will be needed. Finally, we assumed that potential attrition rate may be 20–30% due to the functional decline of the participants.

The IG is composed of home care clients aged 65 years or older who are new participants in the day activity service. All new participants of the day activity service are eligible for the IG. The participants are recruited with the help of personnel who are responsible for the official decisions of the day activity service. Personnel or researchers will call older people in receipt of service decisions to access the day activity service and invite them to participate in the study. Researchers will receive the contact details of the day activity service participants from the personnel. Information about the study, an informed consent form and the first questionnaire are sent to those home care clients who agree to participate in the study when calling them. IG participants fill the informed consent form and baseline survey before beginning to participate in the day activity service.

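### The service is delivered in groups in the intervention arm only, but the sample size assumes independent participants and the analysis text names only within-person correlation

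*Protocol article*

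**What the plan says.** The protocol article describes group delivery under Description of the intervention: "It is a group-based intervention, and the duration of one meeting is from 2 to 6 hours". Meetings are weekly and led by tutors, and content and session length differ between settings. Under Overall study design and setting it adds: "The day activity service is carried out across 12 municipalities, villages, or residential areas". According to Study conduct, CG participants continue with usual home care.

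Under Participants, selection criteria and recruitment, the sample size rests on three inputs: "We accepted an alpha risk of 0.05% and a power of 80% at an effect size of 0.5". The result is: "A theoretical sample of 64 participants in the IG and 64 participants in the CG will be needed". An attrition allowance of 20-30% follows, and the target is 100 per group. No ICC or design effect is given.

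Under Statistical analysis (Quasi-experimental trial), "the data will be analysed using suitable methods for correlated panel data such as mixed effect modelling or generalized estimating equations modelling [30". Propensity score weighting and multiple imputation are to be used if needed. Differences in delivery enter as subgroups (research area, session duration) or, under Process evaluation, by sorting participants according to how their group was tailored.

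**The concern.** IG participants who attend the same group share tutors, activities, session length and each other's company. The primary outcome is social inclusion, and the service aims to create social interaction and peer support, so outcomes within a group can be expected to correlate. CG participants have no corresponding group. This is a partially nested design.

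Two things follow. A sample size worked out for independent people overstates power for any positive ICC. And a panel model whose only level of dependence is the person leaves between-group variance out of the standard error of the treatment effect, so intervals are too narrow and p-values too small. Subgroup analyses by duration or tailoring do not repair this, because they compare types of group and do not allow for correlation within a group.

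**Working it through.** **Inputs.** From the article: standardised effect 0.5, power 80%, 64 per group, attrition 20-30%, target 100 per group, 12 places of delivery. Assumed: the ICC (none is given; 0.05 and 0.10 as working values, 0.01-0.20 as the range) and the number of clusters (12, taken from the number of places; 20 as a sensitivity case, because the number of groups is not stated).

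**Step 1: reproduce 64.** For two-sided 5% and 80% power, n = 2(1.960 + 0.842)² / 0.5² = 62.8, so 63. The exact two-sample t-test gives 63.8, so 64, with power 80.1% (80.7% on the normal approximation). The article speaks of "directional sample size calculations", but a one-sided 5% t-test needs only 51. Alpha read literally as printed (0.0005) needs 153. So 64 is the two-sided 5% figure for independent participants, with no design effect.

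**Step 2: attrition.** 64/0.8 = 80 and 64/0.7 = 91.4, so 92. The target of 100 exceeds both and leaves 80 or 70 completers per group.

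**Step 3: clustering in the IG only.** With n per group and 12 clusters:
- m = n/12 and DE = 1 + (m − 1) × ICC
- variance ratio of the group difference: R = (1 + DE)/2
- type I error if the model omits the group: 2[1 − Φ(1.96/√R)]
- power with the correct standard error: Φ(0.5/√(2R/n) − 1.96)

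Example, n = 70 and ICC 0.05: m = 5.83; DE = 1 + 4.83 × 0.05 = 1.242; R = 1.121; √R = 1.059. Type I error = 2[1 − Φ(1.851)] = 6.4%. Power = Φ(2.958/1.059 − 1.96) = Φ(0.834) = 79.8%.

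| n per group | ICC | DE | √R | Type I error, group omitted | Power |
|---|---|---|---|---|---|
| 64 | 0.05 | 1.217 | 1.053 | 6.3% | 76.6% |
| 64 | 0.10 | 1.433 | 1.103 | 7.6% | 72.7% |
| 70 | 0.05 | 1.242 | 1.059 | 6.4% | 79.8% |
| 70 | 0.10 | 1.483 | 1.114 | 7.9% | 75.6% |
| 80 | 0.05 | 1.283 | 1.068 | 6.7% | 84.1% |
| 80 | 0.10 | 1.567 | 1.133 | 8.4% | 79.7% |

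On the same formula, 80% power needs 71 per group at ICC 0.05 and 81 at ICC 0.10.

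**Step 4: sensitivity.**
- *ICC 0.01 and 0.20, 12 clusters:* power is 79.9% and 65.6% at 64 per group, 83.2% and 68.0% at 70, and 87.7% and 71.4% at 80.
- *20 clusters, ICC 0.05 and 0.10:* at 70 per group, power is 81.9% and 79.6% and type I error 5.7% and 6.5%. At 80 per group, power is 86.2% and 83.9% and type I error 5.9% and 6.8%.
- *Small degrees of freedom (t version, 12 clusters), ICC 0.05 and 0.10:* power is 77.4% and 72.7% at 70, and 81.9% and 76.9% at 80.
- *ICC up to which power stays at 80%, 12 clusters:* about 0.05 with 70 completers and 0.10 with 80. In the t version the limits are about 0.02 and 0.07.

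**Step 5: weighting and baseline adjustment, at 70 per group, 12 clusters, ICC 0.05 and 0.10.** An assumed weighting design effect of 1.3 alone gives 69% and 64%. An assumed baseline correlation of 0.5 (variance × 0.75) alone gives 89.7% and 86.5%. Both together (1.3 × 0.75 = 0.975) give 80.8% and 76.7%. The two roughly cancel, so the table in step 3 is a fair central picture.

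**The case against.** The strongest reply is that the article never says participants are treated as independent. It offers mixed models and GEE as examples of suitable methods. A mixed model can carry a group random effect, and GEE can be clustered at group level. This is a condensed article, and the random-effects structure is commonly left to an analysis plan. A reader might infer that the planned standard errors are wrong as a matter of fact. The text does not support that: the statement holds only if no group level is fitted.

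A reader might also infer that the trial is underpowered. The documents do not support that either. The target of 100 exceeds the 80-92 that attrition requires, and this margin absorbs a modest ICC. Twelve is the number of places, not of groups, and the article describes groups of several durations, so there may be more and smaller clusters. Weighting is only conditional, and baseline adjustment could recover its cost. Finally, the process evaluation plans to use the group each participant attends, so that information may well be collected.

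All of this limits the size and certainty of the point. It does not remove it. The sample size is stated in full and reproduces only under independence. The one form of dependence named is that of panel data. The uses of group information that are described are not adjustments for clustering.

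**Conclusion.** The point holds in conditional form. The stated 80% power at 64 per group makes no allowance for one-arm clustering and is overstated for any positive ICC. For the design as planned, power lies near 80%, somewhat above or below it depending on attrition, the ICC and the number of groups. If the primary model is fitted without a group level, the type I error rises moderately, to roughly 6-8% over ICCs of 0.05-0.10 with 12 clusters and 70-80 completers, and by less with more, smaller groups. The ICC, the use of 12 as the cluster count, the weighting penalty and the baseline correlation are all assumptions. The matter should be corrected before analysis, but it is not a critical fault: nothing irreversible follows provided the group attended is recorded.

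**What to change.** - Record the day activity group attended by each IG participant. The municipalities are to supply participation data after the six-month period, and the group identifier could be requested with them.
- Analyse the primary outcome with a partially nested model: a random intercept for day activity group in the IG only, arm-specific residual variance, a person-level random effect, and a small-sample correction to the degrees of freedom.
- In the cost-effectiveness bootstrap, resample whole groups in the IG and individuals in the CG.
- Restate power as a range over assumed ICCs (for example 0.02-0.10) and numbers of groups, showing the effect of baseline adjustment and of any weighting. Keep the planned enrolment.

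The cost is one extra identifier and some wording in the analysis plan. The downside is slightly wider intervals and a less favourable stated power.

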## Methods

### Overall study design and setting

This mixed method pragmatic quasi-experimental trial will examine the effectiveness, cost-effectiveness, and process of an existing intervention called *day activity service*. The overall study design is described in Fig. 1. The effectiveness is evaluated with quantitative quasi-experimental design by comparing a group of home care clients taking part in the intervention (IG) with a group of home care clients with similar characteristics not taking part in the intervention (CG). The study is a pragmatic trial, as the day activity service is an existing intervention carried out in ordinary circumstances as part of formal home care services [18]. The trial is quasi-experimental, because randomization is not an option due to the fact that the intervention is already in use. Baseline, three-month follow-up, and six-month follow-up surveys are collected from IG and CG participants. The cost-effectiveness evaluation is based on the quasi-experimental trial design and the administrative data of the social and health care service use. The process evaluation is mainly based on qualitative data that is collected by interviewing the IG participants and the professionals working at the day activity service and formal home care.

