#### Statistical analysis

The cost-effectiveness of the intervention will be analysed in relation to home care without day activity service using the incremental cost-effectiveness ratio (ICER) [36]. The ICER indicates between-group differences in costs and outcomes in 3- and 6-months follow-up periods, and will be calculated as follows:$$\textrm{ICER}=\left({\Delta \textrm{C}}_{\textrm{IG}}-{\Delta \textrm{C}}_{\textrm{CG}}\right)/\left({\Delta \textrm{E}}_{\textrm{IG}}-{\Delta \textrm{E}}_{\textrm{CG}}\right)$$

where

∆C_IG_ = change in mean costs in the intervention group.

∆C_CG_ = change in mean costs in the control group.

∆E_IG_ = change in mean effectiveness in the intervention group.

∆E_CG_ = change in mean effectiveness in the control group.

Bootstrap simulation will be conducted to describe the statistical uncertainty related with the observed ICER. The probability distribution of ICER will be examined graphically by cost-effectiveness planes and cost-effectiveness acceptability curves.

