## Discussion

### Strengths and limitations

To our knowledge, this is the first study examining the effectiveness and cost-effectiveness of the day activity service targeted at older home care clients in Finland. Hence, the study offers novel understanding on the possible benefits of this type of intervention in addressing old-age social exclusion. In addition, this is a mixed method trial not only focusing on effectiveness but also evaluating the process of the intervention. Using a mixed methods approach, it is possible to measure effects of the intervention quantitatively, as well as explore experiences of the study participants qualitatively. We argue that it is important to highlight the voices and perceptions of older home care clients in relation to the day activity service.

A limitation of the study is the non-randomization especially in case of challenges on forming the comparison group. The challenge may be to find enough (*n* = 100) home care clients who are lacking social activities such as peer group activities. In addition, non-randomization may cause differences in the main sociodemographic and other background variables between groups at baseline. However, possible differences will be considered in statistical analyses.

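### Adjustment for confounding in this non-randomised comparison is left conditional with no criterion, and no adjustment is named for the ICER, so confounding can remain in both

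*Protocol article*

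**What the plan says.** Under Overall study design and setting, the article states: "The trial is quasi-experimental, because randomization is not an option due to the fact that the intervention is already in use". The two groups arise by different routes. Intervention group (IG) members apply for the service and receive a service decision. Comparison group (CG) members are drawn from a separate survey, starting with respondents who would like to join group activities but do not, and then selected to resemble recent service starters on functioning and health.

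The trial's Statistical analysis section opens: "First, descriptive analyses will be conducted to indicate similarities and differences between baseline characteristics in the IG and in the CG". The tools are chi-square, t and Mann-Whitney tests. Mixed models or GEE follow for the outcomes, with no covariates named, and then: "The challenges of non-randomization will be taken into account using statistical methods, such as propensity score weighting [32], if necessary".

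Under Economic evaluation, Statistical analysis: "The ICER indicates between-group differences in costs and outcomes in 3- and 6-months follow-up periods". The formula divides the group difference in mean cost change by the group difference in mean effect change. Uncertainty comes from a bootstrap, and no weighting or covariate is mentioned.

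Strengths and limitations concedes that "non-randomization may cause differences in the main sociodemographic and other background variables between groups at baseline", and adds in general terms that such differences will be taken into account in the analysis.

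**The concern.** In a non-randomised comparison, control of confounding is part of what identifies the effect. Making it conditional, with no rule for when the condition is met, has two consequences. The primary estimator can be chosen after the data are seen. Imbalances that nobody judges important enough to act on can also pass into the effect estimate. Significance tests are a poor guide here, because a non-significant result with about 100 per group is weak evidence of balance. If the effect estimate is adjusted and the ICER is not, the effectiveness result and the denominator of the ICER could also disagree.

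**Working it through.** **Inputs from the article.** Target 100 per group; theoretical requirement 64 per group; standardised effect 0.5; power 80%; attrition 20–30%.

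**Inputs assumed (not in the article).** A confounder imbalanced by d = 0.2 to 0.3 SD and correlated r = 0.3 to 0.5 with the outcome.

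**Step 1. The plan's own figure.** n per group = 2(1.96 + 0.8416)² / 0.5² = 62.8, so 63 by the normal approximation. The t-test solution is 63.8, so 64, which matches "A theoretical sample of 64 participants in the IG and 64 participants in the CG will be needed". This needs a two-sided alpha of 5%. The printed alpha of 0.05% would need about 150 to 153 per group, so I take 5% as meant. Dropout: 64/0.8 = 80 and 64/0.7 = 91.4, so 92; a target of 100 covers both.

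**Step 2. What a baseline test can see** (two-sided 5% t-test).

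| n per group | Power, d = 0.2 | Power, d = 0.3 | Smallest significant difference, 1.96·√(2/n) |
|---|---|---|---|
| 64 | 20% | 39% | 0.35 SD |
| 100 | 29% | 56% | 0.28 SD |

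At 100 per group, a 0.2 SD imbalance is missed 71% of the time and a 0.3 SD imbalance 44% of the time.

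**Step 3. Bias with no adjustment, one confounder.** Bias = d × r, from 0.2 × 0.3 = 0.06 SD to 0.3 × 0.5 = 0.15 SD. That is 12% to 30% of the planned effect of 0.5.

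**Step 4. Three strategies, one confounder, no true effect** (20,000 simulated trials per row; follow-up outcome only).

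| n | d | r | Bias (SD): never / test-then-adjust / always | Type I error: never / test-then-adjust / always |
|---|---|---|---|---|
| 64 | 0.2 | 0.3 | 0.058 / 0.031 / −0.002 | 6.1% / 5.0% / 4.9% |
| 64 | 0.2 | 0.5 | 0.099 / 0.055 / −0.001 | 8.7% / 5.4% / 4.9% |
| 64 | 0.3 | 0.3 | 0.092 / 0.035 / 0.001 | 8.2% / 5.4% / 4.9% |
| 64 | 0.3 | 0.5 | 0.151 / 0.060 / 0.002 | 13.6% / 6.0% / 4.9% |
| 100 | 0.2 | 0.3 | 0.062 / 0.030 / 0.002 | 6.8% / 5.1% / 4.8% |
| 100 | 0.2 | 0.5 | 0.099 / 0.046 / −0.001 | 10.6% / 5.5% / 4.9% |
| 100 | 0.3 | 0.3 | 0.091 / 0.023 / 0.000 | 9.5% / 5.0% / 4.7% |
| 100 | 0.3 | 0.5 | 0.152 / 0.040 / 0.002 | 18.5% / 6.1% / 5.0% |

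Always adjusting removes the bias in every row. Test-then-adjust leaves 0.02 to 0.06 SD.

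**Step 5. The ICER.** Changes from baseline remove stable level differences between groups. They do not remove differential trends or regression to the mean. If the baseline outcome differs by 0.3 SD for transient reasons and the baseline-to-follow-up correlation is ρ (assumed 0.5 to 0.7), the contrast in change shifts by 0.3 × (1 − ρ). That is 0.15 SD at ρ = 0.5 and 0.09 SD at ρ = 0.7.

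**The case against.** Three stronger readings are tempting, and the article does not support them.

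*The baseline tests decide whether adjustment happens.* A reader might infer this from the order of the text. But the article calls those comparisons descriptive, and the adjustment sentence comes later without mentioning p-values. What stands is that no criterion is given and no other balance assessment is described. The test-then-adjust results therefore illustrate one plausible way of applying the clause, not a stated procedure.

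*The bias could be half the planned effect.* Five independent confounders, each imbalanced by 0.2 SD with a coefficient of 0.25, all in one direction and never adjusted for, give 5 × 0.2 × 0.25 = 0.25 SD. Adjusting only for the significant ones leaves 0.12 SD and a type I error of 12%. Those figures compare follow-up values alone, whereas the plan has baseline, three-month and six-month data. If the same confounders affect baseline and follow-up equally, the unadjusted bias in change is 0.00 SD. If half their effect arises after baseline, it is about 0.12 SD. With baseline as a covariate, 0.05 to 0.09 SD remains in the equal-effect case. The risk is real, but the large figure depends on chosen assumptions.

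*The ICER is fixed as unadjusted.* The formula is a definition and does not exclude weighted means, and the economic evaluation is described as part of the same trial design. What stands is that no adjustment is named there, including in the bootstrap.

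Two further mitigations are fair: the CG is selected for similarity, and the limitations section promises to consider differences. Both reduce the risk. Neither replaces adjustment. The named matching indicators are examples (general quality of life and perceived health) that include neither ESIS nor loneliness, and the promise carries no method or rule. A condensed article may leave the covariate list to a fuller plan, but the conditional clause is stated here and is itself the fault.

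**Conclusion.** The concern holds in this form: the article makes control of confounding optional, without a criterion, in a comparison it acknowledges is not randomised, and names no adjustment for the ICER. Confounding *can* remain in the effect estimate. In the ICER, what can remain is confounding of change, not stable level differences.

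The low power of baseline tests (29% and 56% at 100 per group) follows from the planned sample size alone. The size of any bias rests on the assumed imbalance and correlation. For one confounder it is modest under test-then-adjust, with type I error of 5.0% to 6.1%. It grows if no adjustment is made or if several confounders act together. Whatever its size, the undefined condition leaves the choice of primary estimator open until the data are seen, and that is enough reason to change it.

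**What to change.** - Delete the condition. State that the primary estimate for each outcome is adjusted, whatever the baseline tests show, by propensity weighting or by a covariate-adjusted mixed model or GEE. Choose one in advance.
- Fix the covariates from information already collected or known at baseline: ESIS, loneliness, EUROHIS-QOL, perceived health, ADL/IADL needs, age, sex, cohabitation and research area.
- Judge balance by standardised differences, not p-values.
- Apply the same adjustment to incremental costs and incremental effects, repeating it within each bootstrap sample.
- Report the unadjusted result as a sensitivity analysis.

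No new data are needed. The cost is a change of wording, modest programming and, if weighting is chosen, a smaller effective sample size with wider intervals.
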